#### Expectations

*Side effect expectations* refer to the patients’ cognitive representations of the undesired effects related to a specific treatment. They will be measured with the General Assessment of Expected Side Effects Scale (GASE**-**expect), which is a modified version of the GASE**-**scale [46,47] and was designed to measure patients’ pharmacological response expectations with regard to the 45 most common side effects, including non**-**specific and specific complaints of endocrine therapy. Patients are instructed to indicate if and how strongly they expect to suffer from each potential side effect within the first three months of endocrine treatment.

*Self-efficacy expectations about coping* refer to the degree to which patients believe they are able to manage occurring side effects. They will be assessed using a modified version of the GASE**-**expect. Patients are asked to indicate their coping expectations for each of the 45 listed side effects (i.e., “Will I be able to manage occurring adverse symptoms?”).

*Treatment expectations:* Expectations about medicines in general as well as specific concerns and necessity beliefs about endocrine therapy will be assessed with the German version of the Beliefs About Medicines Questionnaire (BMQ) [19,50]. The BMQ has previously been used to assess medications beliefs in breast cancer patients [52]. Additionally, pre**-**treatment expectations regarding SEPT and ACG will be assessed using single items.

*Illness expectations:* Expectations e.g., about time course, consequences, personal and treatment controllability of breast cancer, will be measured with the brief illness perception questionnaire B**-**IPQ [53]. Each single item represents a scale (in addition to the above mentioned: concerns, emotional response, coherence and aspects of identity). The cause**-**scale was excluded. This questionnaire has previously been used in cancer patients [54]. As suggested, the words “illness” and “treatment” were replaced with “breast cancer” and “endocrine therapy” (Table 2).

### Additional variables

*Fear of progression* will be assessed with the short form of the of the Fear of Progression Questionnaire (PA**-**F**-**K) [55] consisting of 12 statements (e.g., being afraid of disease progression). It has shown good psychometric properties in breast cancer patients [56].

*Anxiety and depression* will be measured with the German Hospital Anxiety and Depression Scale (HADS**-**D) [38,39], which rates the severity of seven symptoms of anxiety and seven symptoms of depression over the past week and was designed for use in persons with physical illnesses. It has shown good psychometric properties in breast cancer patients [57].

*Treatment evaluation* will be measured in both intervention groups (ACG and SEPT). After every session, therapist and patient will rate their satisfaction with the unit using 12 items.

*Knowledge about the patient’s own tumor hormone-receptor status* will be assessed by one item [58].

*Somatosensory Amplification* is the tendency to perceive ambiguous sensory events as unpleasant and will be assessed with the Somatosensory Amplification Scale (SSAS) [59]. The scale consists of 10 items (e.g., “I am often aware of various things happening within my body”) and shows high validity and acceptable reliability in samples with breast cancer [60].

*Partnership quality* will be measured with one single item of the short form of the Partnership Questionnaire (PFB**-**K) [61] with reference to Terman [62] asking “How happy would you rate your partnership at the moment?”, which has been recommended for assessing satisfaction with a partnership.

### Data analysis

Missing values will be replaced using multivariate imputation techniques. A repeated measures multivariate analysis of variances (MANOVA) will be used to analyze treatment effects. To identify predictors of treatment outcome, multiple regression analyses will be conducted. To analyze pathways of the effects, mediator analyzes will be computed. Case studies will be performed to illustrate characteristics of the treatment processes from patients’ und therapists’ perspectives. Level of significance will be set at α = .05.

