**Methods/Design:**

In a randomized controlled trial, 184 female breast cancer patients are assigned to receive either SEPT, standard medical care or a manualized supportive therapy at the start of adjuvant endocrine treatment. SEPT consists of three sessions of cognitive**-**behavioral training including psychoeducation to provide a realistic view of endocrine therapy, imagination**-**training to integrate positive aspects of medication into daily life, and side**-**effect management to enhance expectations about coping ability. Side effects three months after the start of endocrine therapy serve as primary outcomes. Secondary outcomes include quality of life, coping ability and patients’ medication adherence. Patients’ expectations (i.e., expectations about side effects, coping ability, treatment and illness) are analyzed as mediators.

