### Sample size calculation

Required sample sizes were determined a priori with G**-**Power [37]: The sample size for the randomized group comparison was determined according to a MANOVA with repeated measures, testing for a three groups x three time points interaction. Assuming a medium effect size of f(V)=.20, N=153 patients (n=51 per group) are needed to achieve 80% power.

Taking into account a potential drop**-**out rate of 20% (e.g., due to exhaustion or medical complications), we aim to include a total of 184 breast cancer patients.

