### Quality standards (Minimization of bias)

#### Randomization and blinding

Randomization follows after completing baseline assessment. Patients are equally allocated to one of the three treatment arms using sealed envelopes. Assignment follows a stratified permuted block randomization procedure with a block size of nine. Stratification criteria (2×2) are the sum score (≤13 vs. >13) of the hospital anxiety and depression questionnaire (HADS**-**D) [38,39] during hospital stay and type of medication (aromatase inhibitor vs. tamoxifen). Assignment sequence is generated by staff who are not involved in the intervention process and conducted electronically using the statistical program WINPEPI [40]. The research assistants responsible for the assessment are blinded to group allocation.

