### Attention control group (ACG): *supportive therapy*

Supportive therapy serves as an attention control group for non**-**specific factors such as therapist’s attention and patient**-**therapist relationship. It serves to distinguish specific effects of SEPT from psychological placebo effects [43]. Supportive therapy [44] as a manualized, non**-**specific psychological intervention has been previously used in clinical trials [45]. It includes common factors such as elicitation of affect, treatment context, empathy, reflective listening, and feeling understood. It will be delivered in the same frequency and on the same occasions as SEPT (three individual sessions and three booster calls).

*Sessions 1, 2 and 3:* In the supportive therapy session contents may vary; there are no specific topics therapists need to address, there is no patient material and no homework. Nevertheless, every session can be structured into three phases: the beginning, the therapeutic dialog and the end. At the beginning patients are asked about relevant themes they want to talk about. During the therapeutic dialog patients lead the session and the therapist follows, while concentrating especially on the validation of patients’ affects. It is suggested to talk about any topics that appear to have an affective valence to the patients. The therapist focuses on creating a warm atmosphere and shows empathy and unconditional positive regard towards the patient. At the ending of all sessions all themes are reviewed with the focus on the affect of the individual patient.

In the control group booster calls are conducted simultaneously to those in the intervention group, but they do not follow a particular structure. Patients are asked about their feelings since the last session.

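### The 80% power belongs to an omnibus group-by-time MANOVA interaction, which does not test whether SEPT beats standard care or the attention control

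*Protocol article*

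**What the plan says.** Sample size calculation (protocol article) sizes the trial on a repeated-measures MANOVA "testing for a three groups x three time points interaction". The result is: "Assuming a medium effect size of f(V)=.20, N=153 patients (n=51 per group) are needed to achieve 80% power".

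Data analysis names one method for treatment effects: "A repeated measures multivariate analysis of variances (MANOVA) will be used to analyze treatment effects". One significance level is given: "Level of significance will be set at α = .05". Regression and mediator analyses are listed for other purposes. The word interaction appears only in the sample size paragraph, so the powered test is read from the two sections together.

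The aims are specific to arms. Of the attention control the protocol says: "It serves to distinguish specific effects of SEPT from psychological placebo effects". The Discussion says that SEPT is compared with both the attention control group (ACG) and standard medical care (SMC).

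On timing, the abstract says: "Side effects three months after the start of endocrine therapy serve as primary outcomes". The Discussion gives three and six months as primary.

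**The concern.** A group-by-time interaction with three arms and three visits has 4 degrees of freedom. It rejects for any departure from parallel mean profiles, whichever arm departs, in whichever direction and at whichever follow-up. The trial's claim is narrower: SEPT lowers side effects against standard care, and does so by more than therapist attention does.

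The third arm exists to support the second half of that claim. If supportive therapy works as well as SEPT, or if it alone works, the interaction is still likely to be significant. A report that took this as evidence for SEPT would make the very inference that the attention control was added to prevent. The stated 80% would also be read as power for SEPT's effect, which it is not.

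**Working it through.** **Inputs from the protocol.** f(V) = .20, N = 153, 51 per group, 80% power (Sample size calculation); α = .05 (Data analysis); equal allocation (Randomization and blinding).

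**Assumptions not in the protocol.** Normal scores with equal SDs; equal correlation ρ between all pairs of visits, taken as .5 and .6; effects constant over three and six months unless stated; 0.5 SD as an illustrative effect.

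**1. Reproduce N = 153.** For the Pillai interaction test with k = 3 groups and m = 3 times, s = 2:
- df1 = (k−1)(m−1) = 4
- df2 = 2(N−3) = 300
- λ = s·N·f² = 2 × 153 × .04 = 12.24
- Power = .804. The smallest N that is a multiple of 3 and reaches 80% is 153.

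The figure reproduces, so the 80% is power for the omnibus interaction.

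**2. Omnibus power when SEPT and ACG are equally 0.5 SD better than SMC.** The test acts on the two changes from baseline. Their covariance has 2(1−ρ) on the diagonal and (1−ρ) off it. For a constant effect, q = (2/3)/(1−ρ). The variance of the group pattern (0, −1, −1) is 2/9. Then ω = δ²·(2/9)·q, V = ω/(1+ω), f² = V/(2−V) and λ = 306·f².

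| ρ | q | ω | V | λ | Power |
|---|---|---|---|---|---|
| .5 | 1.333 | .0741 | .0690 | 10.93 | .75 |
| .6 | 1.667 | .0926 | .0847 | 13.54 | .85 |

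The pattern with only ACG better, (0, 0, −1), has the same variance of 2/9, so its omnibus power is the same. Simulation (3,000 trials per scenario) agrees: 75–76% at ρ = .5 and 85–86% at ρ = .6 across the two patterns. When SEPT equals ACG, the interaction is significant while SEPT versus ACG at three months is not in about 71–73% of trials (ρ = .5) and 80–81% (ρ = .6). When only ACG works, SEPT versus SMC is significant in about 5%, the chance level.

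**3. Power for SEPT versus ACG at the planned f(V) = .20.** Here V = 2 × .04/1.04 = .0769 and ω = .0769/.9231 = .0833. At ρ = .5, δ = √(.0833/(v × 1.333)), where v is the variance of the group pattern.
- SEPT alone works: v = 2/9, so δ = .53 SD.
- ACG midway between SEPT and SMC: v = 1/6, so δ = .612 SD from SMC to SEPT and .306 SD from ACG to SEPT.

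A baseline-adjusted three-month contrast has residual SD √(1−.25) = .866 and noncentrality (difference/.866) × √(51/2):
- .53/.866 × 5.05 = 3.09, power about 86%
- .306/.866 × 5.05 = 1.78, power about 42%

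Omnibus power is about 82% in both cases by simulation. The same omnibus figure therefore goes with very different power for the decisive contrast.

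**4. Timing.** At f(V) = .20 and ρ = .5, a difference at six months only makes the interaction significant in about 81% of trials, while each three-month SEPT contrast stays near 5%.

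**5. Detectable pairwise difference with 51 per arm, 80% power, two-sided .05.** Unadjusted: 0.56 SD. Baseline-adjusted, 0.56 × √(1−ρ²):
- ρ = .3: 0.56 × .954 = 0.53 SD
- ρ = .5: 0.56 × .866 = 0.49 SD
- ρ = .7: 0.56 × .714 = 0.40 SD

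**The case against.** The strongest reply is that this is a condensed article. Contrasts, their order and the handling of α commonly stand in a full protocol or SAP. That is right. A reader might infer that the pairwise comparisons are unplanned and have no error control, but the document's silence does not support this. Moreover, with three arms, a significant omnibus test followed by the same test for each pair at .05 is a closed procedure. In simulation with no effects at all, the omnibus test plus any three-month contrast was significant in about 3% of trials. Control is incomplete for a three-month claim: with a difference at six months only, that rate is about 11–12%. Incomplete is not absent.

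A reader might also infer that the trial is too small for its contrasts. The figures do not show that. If SEPT beats both comparators by 0.5 SD, each adjusted contrast has about 82% power at ρ = .5.

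Nor does the efficiency of baseline adjustment carry the point. With only SEPT working at 0.5 SD, omnibus power is 74–76% against about 82% per adjusted contrast at ρ = .5, but about 86% against 88% at ρ = .6. Winning both contrasts has about 72–73% at ρ = .5, no better than the omnibus.

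Two further limits stand. If SEPT and ACG both beat SMC, SEPT does beat standard care; what fails is specificity. And rejecting on a six-month difference is a fault only under the abstract's primary time point, not under the Discussion's.

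What remains is what the protocol itself fixes: its power, and its one named test of treatment effects, rest on a hypothesis other than the one it asks. An unseen document could add contrasts, but the published 80% would still belong to the interaction.

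**Conclusion.** The point holds as a mismatch between the test and the question. N = 153 is correct for the interaction. A significant interaction does not show a SEPT-specific effect: it would occur in about 75–85% of trials if SEPT and supportive therapy were equally effective at 0.5 SD, and equally often if only supportive therapy worked. The stated 80% does not transfer to SEPT versus ACG, where power at the planned f(V) runs from about 86% to about 42% depending on where the attention control falls.

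The sizes rest on normal data, equal SDs and assumed correlations (.5–.6 for the omnibus rates, .5 for the contrast power). The logical point does not depend on them. It also holds under either primary time point, since the interaction isolates no SEPT comparison at three months or at six.

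**What to change.** 1. Reconcile the primary time point: three months in the abstract, three and six months in the Discussion.
2. Make the primary analysis a baseline-adjusted comparison of GASE at that time point. Use ANCOVA, or a mixed model with three- and six-month GASE as responses and baseline GASE as covariate.
3. Name SEPT versus SMC and SEPT versus ACG as the confirmatory contrasts, with a stated familywise rule. A fixed sequence at two-sided .05 is one option; other orders or an α split would also serve. If these contrasts already stand in another document, bring the protocol's analysis and power statements into line with it.
4. Keep the group-by-time interaction as supportive.
5. Restate power for the contrasts: with 51 per arm, a detectable difference of about 0.56 SD unadjusted, or about 0.53, 0.49 or 0.40 SD adjusted at assumed baseline correlations of .3, .5 or .7.

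The cost is analysis-plan wording and a rewritten power statement, with no new data or visits. Under a fixed sequence the second contrast can be claimed only if the first succeeds. The restated power may also look less favourable than the present 80%, above all if supportive therapy has some effect.

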### Baseline demographic data

Preliminary baseline demographic data was assessed in N = 55 participating women with a primary breast cancer diagnosis. On average patients were 54.8 years old (SD=8.2, range=39-71 years), and mostly married or living with a partner (61.8%). Other patients were single (12.7%), widowed (5.5%) or divorced (20.0%). The majority of patients had primary education (63.6%), other patients finished secondary education (16.4%) or university education (20.0%).

More than half of the patients were diagnosed with stage I breast cancer (69.1%), further 27.2% of patients were diagnosed with stage II and additional 3.6% with stage III. Most patients (89.1%) received breast conserving therapy and only 10.9% mastectomy. A large group of patients (69.1%) was scheduled to undergo first-line endocrine treatment with tamoxifen (+/− GnRH-analoga). A third generation aromatase inhibitor (i.e. anastrozole, letrozole or exemestan) was recommended to the other patients (30.9%).

## Discussion

Although expectations have been found to predict the occurrence of side effects in cancer patients, this study presents the first randomized controlled trial evaluating a short**-**term cognitive**-**behavioral intervention to prevent side effects during adjuvant endocrine therapy by optimizing breast cancer patients’ expectations. The side**-**effect prevention training (SEPT) is compared with an attention control group (ACG) receiving supportive therapy and a standard medical care group (SMC) receiving standard treatment for breast cancer patients and additional oral and written information about adjuvant endocrine treatment. The primary outcomes are the occurrence of side effects three and six months after the start of intake of endocrine therapy. Further beneficial effects for quality of life, coping ability and adherence to medication are evaluated. Patients’ response expectations, expectations about coping ability and expectations about treatment and illness are analyzed as mediators. The study also gives some insights into characteristics of patients who benefit the most from SEPT and of patients at high risk of developing side effects.

If SEPT is found to be effective, it could be integrated into daily clinical practice. Effects of preventing non-specific symtoms and nocebo side effects may improve the quality of life during treatment, lead to better medication adherence, and thereby may help to reduce progression and mortality in breast cancer patients and decrease costs of treatment. The training could be delivered into health care settings and applied by trained and supervised health care professionals. In addition, the study will provide insights into pathways of clinical nocebo effects and non**-**specific side effects that may be applicable to other fields of illness and medication.

The study has some limitations that need consideration. First, our study design does not allow complete control regarding information patients may receive from their gynecologists about side effects of endocrine treatment, coping possibilities and about what happens while patients are in rehabilitation clinics. Another problem is that the study does not include patients who decide to start endocrine therapy before the baseline measurement. Presumably, patients in this group experience the strongest feelings of anxiety of progression and have more negative illness beliefs. This study does not provide conclusions about the efficacy of single treatment elements or differential indications. If treatment effects are robust, future studies are needed to analyze the particular influences of those factors.

The optimization of expectations might be a promising pathway to improve patients’ quality of life during medication intake. So far, this is the first study investigating a psychological prevention program for side effects with the explicit focus on patients’ expectations. The results will provide implications for a possible integration of evidence**-**based prevention training into clinical practice.

## Abbreviations

ACG: Attention control group; AET: Adjuvant endocrine therapy; ER/PR: Estrogen receptor/ progesterone receptor; BCT: Breast**-**conserving therapy; GnRH: Gonadotropin**-**releasing hormone; SEPT: Side**-**effect prevention training; SMC: Standard medical care.
